### Explanatory variables: IC composite index (ICI)

An IC composite score or index (IC index or ICI) will first be created, as suggested by Gutiérrez-Robledo et al. (2019). This score aims to express a summary measure of impairments for an older adult. Initially, each continuous or ordinal subdomain measure will be dichotomized based on acceptable cut-off points to create a binary variable of 0 or 1 (see Table 3 for cutoff points across all subdomain measures). Within a domain, the values of these recoded subdomain measures will be summed up to create a “subdomain score.” The subdomain scores will range from 0 to 2 for the four subdomains with only two measures and from 0 to 6 for the subdomain with six measures (i.e., vitality). Then, each domain of the five IC components will be subdivided into three categories based on the sum of the scores of its subdomains, with the following numerical score: no impairment = 0, mild impairment = 1, and severe impairment = 2. For example, the four domains with only two subdomain measures (e.g., cognitive with subdomain measures memory and cognitive) will be coded 0 if their subdomain score (sum of their subdomain measure) is 0, 1 if the subdomain score value is 1, and 2 if the subdomain score value is 2. The domain with six subdomain measures, vitality (subdomains comorbidity, medication, biomarkers, pain, strength, and nutrition), will be coded 0 if its subdomain score is 0, 1 if the subdomain score is 2–4, and 2 if the subdomain score is 5–6. Scores for each of the five domains will be summed up to produce a composite IC index ranging from 0 (best possible ICI) to 14 (worst possible ICI).

Subsequently, this baseline ICI will be classified in four ways. First, using the terciles of ICI (TIC), ICI values less than or equal to the first tercile (Q1) will be classified as low TIC; ICI values between Q1 and the third tercile (Q3), including Q3, will be classified as medium TIC; and ICI values above Q3 will be classified as high TIC. This analysis model is explicitly shown in Figure 1.

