Second, the change in the ICI value during the follow-up time in the cohort will be measured and referred to as “ICI delta” (∆IC). The ∆IC is calculated as the difference between the ICI measured in the last follow-up wave minus the ICI measure at the baseline (variable with values between 0 and 10). Third, we will consider the presence of a decline in IC (DIC) if one or more declines in an IC domain are found from the baseline measure. As an example of IC domain decline in the cognitive dimension, a Montreal Cognitive Assessment (MoCA) score of 22 at follow-up versus 27.0 at baseline is considered a decline and probable “dementia” (Nasreddine et al., 2005). The opposite will be classified as no decline.

Finally, a weighted measure of IC (WIC) will be derived from the multivariate regression result of the association between IC subdomains and IADL loss, which will be adjusted for individual sociodemographic factors (see the Analysis section below for detailed description of WIC).

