## Research questions and hypotheses to test

This proposed research will answer three scientific questions:1. Whether IC will decrease as expected at the 3-year follow-up (ICI at end-time ≤ ICI at baseline, or ∆IC < 0), regardless of the socioecological context, individual sociodemographic, behavioral, and clinical factors, and comorbidities (Charlson et al., 1987). This research will statistically test the hypothesis that ICI will not change over time (i.e., follow up IC = baseline IC, or ∆IC = 0).2. If DIC (or TIC) at baseline will be a strong predictor of FA, such as ADL (Mlinac and Feng, 2016), IADL (Hokoishi et al., 2001), falls (Kitcharanant et al., 2020), and death, regardless of the socioecological context, individual sociodemographic, behavioral, and clinical factors, and comorbidities (Charlson et al., 1987). That is, whether the proportion of these ADL/IADL losses, falls, and deaths will be greater in the decline group (e.g., DIC present) than in the unexposed group (e.g., DIC absent). Research will statistically test the hypothesis that there is no association between IC and ADL (or IADL) (e.g., relative risk for TIC or DIC and IADL = 1).3. Whether IC and its five domains are directly associated with a measure of QoL (i.e., World Health Organization Disability Assessment Schedule 2.0 (WHODAS 2.0)) (Prüss-Ustün et al., 2017) and LTPA (i.e., the International Physical Activity Questionnaire (IPAQ)) (Craig et al., 2003), regardless of the socioecological context, individual sociodemographic, behavioral, and clinical factors, and comorbidities (Charlson et al., 1987). Research will statistically test the hypothesis that there is no association between IC and either QoL or LTPA (e.g., relative risk for TIC or DIC and LTPA = 1).

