#### Statistical models to assess whether IC is a predictor of ADLs/IADLs, falls, and death

Two Cox regression models will be evaluated to estimate the incidence rates of outcomes (i.e., functional loss measured by IADLs, falls, and death) associated with IC at baseline (e.g., TIC, DIC, and WIC) (ElHafeez et al., 2021). Cox’s first model has the indicator variable X to denote the association with each of the two groups of IC exposure at baseline (e.g., X1 = 1 for medium and high TIC and X1 = 0 for low TIC), with Y being the adverse incident at 3 years of follow-up (loss of ADLs/IADLs, falls, and death); survival times will be measured by the interval from the first assessment to the adverse incident. For subjects who do not experience an adverse incident, the follow-up time will be the last evaluation of the study.

The model also comprises a collection of covariates V with the potential to be a confounding factor in the association between Y and X (e.g., sociodemographic factors), and W would be the potentially interactive term between X and V (e.g., sex * TIC). The regression coefficient of X describes the effect of TIC on outcome Y, that is, the risk of greater or lesser loss of ADL/IADL, falls, and death for those exposed to medium or high TIC relative to those exposed to low TIC. The W terms will assess whether there is a positive interaction between TIC and one of the V confounders that have been identified to be potentially interacting. The model will extend by substituting TIC for DIC or WIC as the main exposure variable X. Alternatively, we can also model Y (e.g., IADL) as a function of X (either TIC, DIC, or WIC) and the same set of V and W using logistic regression to estimate the odds ratio of the outcomes.

We will evaluate the IC trajectory through changes in IC scores (∆IC or WIC) or the presence of IC decline (DIC) after 3 years, along with their associations with IADL outcomes, falls, and death. For example, the mean/median of ∆IC (or WIC) and the prevalence of DIC will be generated at baseline and at the end of the 3-year follow-up. We will then generate the mean/median or prevalence of IC measure by levels of ADL/IADL, falls, and death. The means/medians of IADLs and the incidence of falls and death after 3 years of follow-up will also be estimated.

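### When decline in IC (DIC) is the exposure, the outcome models drop baseline IC and do not name it as a covariate, so the DIC estimate may be confounded in an unknown direction

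*Protocol article*

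**What the plan says.** All references are to the Protocol article.

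- **Exposure.** The section on models for ADLs/IADLs, falls and death first defines X from baseline TIC, then states "The model will extend by substituting TIC for DIC or WIC as the main exposure variable X". Read literally, that phrase could mean the reverse swap. The logistic sentence settles it: the outcome is modelled "as a function of X (either TIC, DIC, or WIC) and the same set of V and W using logistic regression".
- **Covariates.** V is described as "a collection of covariates V with the potential to be a confounding factor in the association between Y and X (e.g., sociodemographic factors"), an open list with a single example. Research question 2 wants the association to hold "regardless of the socioecological context, individual sociodemographic, behavioral, and clinical factors, and comorbidities". Neither names baseline IC.
- **DIC.** The section on the IC composite index will "consider the presence of a decline in IC (DIC) if one or more declines in an IC domain are found from the baseline measure". Each domain is scored "no impairment = 0, mild impairment = 1, and severe impairment = 2".
- **Hypothesis.** Research question 2 asks "whether the proportion of these ADL/IADL losses, falls, and deaths will be greater in the decline group (e.g., DIC present) than in the unexposed group".
- **Assumed effect of poor IC.** Table 1 uses RRs of 1.91, 1.7 and 3.0 for functional loss. Table 2 uses 1.66, 1.3 and 2.0 for death.

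**The concern.** A change-from-baseline exposure is tied to the baseline value by construction. If baseline level also predicts the outcome, a model with change alone mixes the effect of declining with the effect of where the person started.

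The plan's own sample size premise supplies the link to the outcome. The scoring makes a link to the exposure likely: on the 0 to 2 scale, a domain already at 2 cannot be recorded as worse.

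In this plan, baseline IC level enters the outcome models only as X. Once DIC takes that place with an unchanged covariate set, the level is gone. The comparison of decliners with non-decliners in research question 2 could then reflect different starting levels, and the DIC coefficient could not be read as the effect of decline at a given starting level.

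**Working it through.** **1. Check the source of the risk ratios.** Table 1, average column: p1 = 0.0495, p2 = 0.0495 × 1.91 = 0.0945, two-sided α 0.05, power 0.80, unpooled variance:

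n = (1.960 + 0.842)² × [p1(1 − p1) + p2(1 − p2)] / (p2 − p1)² = 7.849 × 0.13266 / 0.002029, which rounds up to 514 per group, as printed. The same formula returns the printed 816, 926 and 3,922. The high-RR columns come out at 140 and 449 against 138 and 432 printed, which does not matter here. The tables serve only as the source of the RR for poor IC.

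**2. Size of the confounding.** For a binary baseline level and multiplicative risks:

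apparent RR = true RR × [1 + a(R − 1)] / [1 + b(R − 1)]

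Here R is the RR for poor baseline IC, a is the share with poor baseline IC among those with DIC, and b is that share among those without.

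- From the plan: R = 1.91 and 3.0 (Table 1), and 1.3 (the lowest value in Table 2).
- Assumed, because the protocol gives no figures: one third have poor baseline IC; P(DIC) is 0.40 with better baseline IC and 0.20 to 0.60 with poor baseline IC; the true RR of DIC is 1.91.

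Worked case, R = 1.91 and P(DIC | poor) = 0.20:
- P(DIC) = (1/3)(0.20) + (2/3)(0.40) = 0.333
- a = 0.0667/0.333 = 0.20; b = 0.2667/0.667 = 0.40
- factor = (1 + 0.20 × 0.91)/(1 + 0.40 × 0.91) = 1.182/1.364 = 0.867
- apparent RR = 1.91 × 0.867 = 1.66

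| P(DIC given poor IC) | Factor, R = 1.3 | Factor, R = 1.91 | Factor, R = 3.0 | Apparent RR, R = 1.91 | Apparent RR, R = 3.0 |
|---|---|---|---|---|---|
| 0.20 | 0.946 | 0.867 | 0.778 | 1.655 | 1.486 |
| 0.30 | 0.974 | 0.935 | 0.890 | 1.785 | 1.700 |
| 0.40 | 1.000 | 1.000 | 1.000 | 1.910 | 1.910 |
| 0.50 | 1.025 | 1.065 | 1.114 | 2.034 | 2.128 |
| 0.60 | 1.050 | 1.132 | 1.238 | 2.163 | 2.365 |

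With half the cohort at poor baseline IC, the extremes at R = 3.0 are 0.778 and 1.222. If DIC had no effect, the apparent RR would equal the factor itself.

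**3. Which side of 1?** Take five domains, k of them already at 2, and an equal chance q of decline in each of the others: P(DIC) = 1 − (1 − q)^(5 − k). With an assumed q = 0.10:
- k = 0: 0.41
- k = 1: 0.34
- k = 2: 0.27
- k = 3: 0.19

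The cap alone therefore pushes the factor below 1. It is cancelled when the per-domain chance in people with k severe domains reaches 1 − (1 − 0.10)^(5/(5 − k)):
- k = 1: 0.123
- k = 2: 0.161
- k = 3: 0.232

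Above those values the factor exceeds 1. The protocol gives nothing to choose between the two cases.

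**4. Effect of adjustment.** In step 2 the RR within each baseline level is 1.91 by construction, in every row. Conditioning on baseline level removes this confounding whichever way it runs.

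**The case against.** **The covariate set is open.** V covers potential confounders of whatever X is, and baseline IC fits that description when X is DIC. Clinical factors and comorbidity are named in research question 2, and the number of chronic morbidities is itself a vitality item in Table 3. An unseen analysis plan could list baseline IC. This stands in part: the accurate word is unspecified, and some overlap exists. But the protocol fixes a rule, one IC measure at a time with unchanged V and W, and that rule as written removes the baseline level.

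**A reader might infer that the effect of decline is underestimated.** The documents do not support this. It requires poor baseline IC to make a recorded decline less likely, and no figure says so. An illustration that gives everyone the same chance of new impairment builds that direction in. The cap is also weaker than it looks. The worked example of decline uses MoCA scores of 27 and 22. That fits a change in the raw score as well as a crossing of the Table 3 cut-off at 25, and if decline is judged on raw measures, most of the cap disappears. The Eligibility section appears to exclude people with CDR above 0, so the cognitive domain could not start at 2.

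**A reader might infer that objectives 5 and 6 ask whether decline adds information beyond baseline IC.** They ask for the trajectory's predictive power and for monitoring of change. The case for adjustment rests on confounding and not on those objectives.

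**Conclusion.** The point holds as a specification fault of unknown direction. When DIC replaces TIC, baseline IC is not specified as a covariate, although the plan treats poor IC as a strong predictor of outcome and defines DIC relative to baseline. On the assumed grid the confounding factor is about 0.78 to 1.24, so a true RR of 1.91 could appear as anything from about 1.49 to 2.36. At R = 1.3 the factor stays within about 5% of 1 in the table. These sizes rest on assumed decline probabilities and multiplicative risk; only the RRs for poor IC come from the protocol. Neither a bias toward the null nor a single magnitude can be claimed.

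Adjustment is worth making because it is cheap and does not depend on the direction. It leaves a separate fault untouched. The same section lists DIC among the baseline IC measures and starts survival time at the first assessment, yet its trajectory paragraph places DIC after 3 years. People who die before reassessment have no DIC, and a decline may follow the event. Adding a covariate does not cure that.

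**What to change.** In the section on models for ADLs/IADLs, falls and death, replace the substitution rule for DIC with a statement that, when DIC or ∆IC is the exposure, baseline ICI is kept in both the Cox and logistic models as a covariate and the coefficient for decline is reported conditional on it.

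Use ICI rather than TIC. ICI runs from 0 as best, so the lowest tercile, labelled low TIC, is the best group, whereas the sample size section treats low IC as the exposed group. Those labels need reconciling before TIC can serve as an adjustment variable.

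The cost is one sentence and one covariate that is already collected. The small downside is that the coefficient must be read at a given baseline IC. The timing of DIC needs its own correction.

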### Objectives

The cohort study proposed here addresses the determinants of IC and its relationships with FAs that allow longevity with good health and independence in everyday life. Considering that the literature on cohort studies that indicate IC values for the different aging trajectories is limited, we intend to build an IC index composed of the different domains, which can be validated as a risk indicator for classic outcomes such as hospitalization, falls, death, and severe dependence. We also intend to use the data to design clinical trials and nested case–control studies, with sample power, to evaluate measures aimed at preventing or mitigating functional ability losses over time.

To that end, we aim to1. Create a population cohort of people aged 60+ (LONGFUN) living in a middle-class neighborhood in a large urban center in Brazil.2. Create a composite IC index considering the five domains: cognitive, psychological, sensory, locomotor, and vitality.3. Carry out an epidemiological segmentation considering the index composed of IC and the sociodemographic, behavioral, and clinical factors.4. Identify the genetic and immunological biomarkers associated with each segment in a representative subsample of the cohort to be evaluated by a geriatric and multidisciplinary team that will define the needs of care for each segment.5. Analyze the trajectory of the IC composite index for the total cohort and for each segment created, seeking its predictive power as an indicator of risk for the main outcomes: hospitalization, disability, falls, and death.6. Monitor IC changes over time and the impact of the changes on baseline predictors.7. Propose strategies for the development of an integrated system for people-centered healthcare based on the identified needs for care.

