### Eligibility

All adults aged 60 and older living in the study area who will be contacted by the study team can participate in the study. Older adults residing in long-stay institutions for the elderly and those who are bedridden will be excluded from our study as the focus of this research is the follow-up of IC until the development of one or more outcomes: severe dependence, fall, hospitalization, or death as a function of IC. It will also be important to ensure through an initial in-house geriatric assessment that participants at baseline do not have significant loss of independence in the activities of daily living (ADL and IADL scores >0) (Katz and Akpom, 1976; Lawton and Brody, 1969) and cognitive ability (Clinical Dementia Rating (CDR) > zero) (Morris, 1994).

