## Dependent variables

• Need for help in ADL (Katz and Akpom, 1976) and IADL (Lawton and Brody, 1969).• Falls in the last year.• Hospitalizations in the last year.• Deaths.

Explanatory variables: IC domains and subdomain measures.

The IC subdomain measures, their levels, cut off points for a binary classification, and references are presented in Table 3.

**TABLE 3 T3:** Intrinsic capacity domains and subdomains measures with classification cut-offs.

Domain	Subdomain	Classification (binary: 0 or 1)	References
Vitality	Number of chronic morbidities	<2 = 0 | ≥ 2 = 1	Charlson et al. (2022) and Charlson et al. (1987); Kim et al. (2021)
	Number of medications taken daily	0–4 = 0 | 5+ = 1	Golchin et al. (2015)
	Handgrip strength	Men:<=36.2 kg = 0 | > 36.2 kg = 1; Women:<=23.0 kg = 0 | > 23.0 kg = 1	Amaral et al. (2019), Alqahtani et al. (2019)
	Body mass index	≤ 25 = 0 | > 25 = 1	Kiskaç (2022), Krzyminska-Siemaszko et al. (2014)
	Biomarkers of metabolism and inflammation	NL = 0 | high = 1	Liu et al. (2017), Bautmans et al. (2022), Bohannon (2019)
	Pain numerical rating scale (NRS)	≤ 6 = 0 | > 6 = 1	Devin and McGirt (2015), Atisook et al. (2021)
Mobility	Tandem stance	Tandem stance for>=10 s = 0 | tandem stance for <10 sec= 1	Joo et al. (2021)
	Gait (timed up and go)	<6 min = 0 | ≥ 6 = 1	Herman et al. (2011); Alexandre et al. (2012)
Sensory	Community screening for visual impairment	Good = 0 | impaired = 1	Clarke et al. (2018)
	Hearing screening in older adults	Good = 0 | impaired = 1	https://hign.org/consultgeri/try-this-series/hearing
Cognitive	Memory (MOCA)	≥ 25 = 0 | < 25 = 1	Nasreddinne et al. (2005)
	Cognitive abilities (CDR)	0 = 0 | ≥ 0,5 = 1	Morris (1994)
Psychological	Depressive symptoms (GDS)	<5 = 0 | ≥ 5 = 1	Almeida and Almeida (1999), Yesavage et al. (1983)
	Sleep quality	good = 0 | bad = 1	Smyth (2013)

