In contrast, we should also be able to model Y as ∆IC (ordinal variable with values from 0 to 10) as a function of a main vector X (IADL, falls, or death) and a collection of parameters V and W similar to the previous model, but using a multivariate ordinal regression model with a latent variable specification, where composite probability methods are applied to estimate model parameters (Hirk et al., 2019).

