## Discussion

There are several reasons for proposing a prospective cohort for the over-60 aged population of São Paulo, Brazil. First, given the rapid aging and the increase in functional limitation among most of the elderly populations in Brazil and the world, it is necessary to better understand the implications of various measures that compose IC and IC itself for the multiple factors that impact on loss of functionality at old age, including preventive and curative actions (Rosa et al., 2003; Costa Filho et al., 2018).

Second, the measure of aging promoted by WHO—IC—has been well-studied in Europe and North America, but the sole study of IC in Latin America did not include Brazil. Brazil has the largest and fastest growing population that is 65 years of age and older in Latin America and the world, and it is predicted to be the fourth largest in the world by 2050. In addition, the complex mix of racial, ethnic, socioeconomic, and environmental factors among urban older populations in Brazil are not easily found elsewhere and provide a fertile ground for exploring multifactorial causes of changes in IC and functional limitations.

Moreover, cohort studies are the strongest methodology for observational epidemiological designs that allow for ethical investigation of IC and its associated events. In this design, all relevant variables and related factors identified in advance can be measured without error and recorded (Andrade, 2022). The design allows for the investigation of multiple outcomes for selected or rare number of exposures. In addition, the cohort study guarantees the maintenance of a temporal sequence between exposure to risk or protective factors and healthcare outcomes, while allowing for the calculation of incidence rates. In addition, prospective cohort studies allow the inclusion of other studies that take advantage of the already formed cohort, such as nested case–controls, and the identification of cohort subsets to evaluate interventions in a randomized intervention trial.

Our proposed prospective cohort study, aiming to evaluate hypotheses about the effect of IC on ADL, IADL, and WHODAS and their progression over time in an older population of São Paulo, Brazil, will be only the second such study to include a Latin American population.

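### Objective 6 is worded backwards in time, and the optional ∆IC regression takes follow-up events as its main predictors, so neither can identify what drives IC decline

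*Protocol article*

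**What the plan says.** Objective 6 (Objectives) reads "Monitor IC changes over time and the impact of the changes on baseline predictors".

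Under the heading on the IC composite index, ∆IC is "the difference between the ICI measured in the last follow-up wave minus the ICI measure at the baseline". The Rationale plans assessment at baseline and after 3 years.

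The section on models for IC as a predictor first sets up Cox models with baseline IC as exposure, "with Y being the adverse incident at 3 years of follow-up (loss of ADLs/IADLs, falls, and death"). Its last paragraph turns this round. IC change becomes the outcome: "we should also be able to model Y as ∆IC (ordinal variable with values from 0 to 10"). The events move to the other side of the equation, because this outcome is to be modelled "as a function of a main vector X (IADL, falls, or death"), with covariates and interaction terms as before. It does not say when X is measured.

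Two other places bear on the timing of X. Eligibility aims to ensure that "participants at baseline do not have significant loss of independence in the activities of daily living (ADL and IADL scores >0"). The list of dependent variables gives "Falls in the last year" without naming the wave.

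**The concern.** A value fixed at baseline cannot be altered by a change that happens afterwards, so objective 6 cannot be answered as it stands.

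The ∆IC regression has a related fault. The study says that it addresses the determinants of IC, and this is the only model with ∆IC itself as outcome. Its main predictors are the events that the study elsewhere treats as consequences of low IC. If they occur in the same three years over which ∆IC is measured, a non-zero coefficient may mean that the event lowered IC, that falling IC led to the event, or both. The Rationale intends the results to inform later intervention studies. A consequence of decline read as its cause would misdirect them.

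**Working it through.** The plan gives no figure that depends on this point, so there is none to reproduce. The check is of time order, followed by illustrations on assumed inputs.

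**1. When can each element of X occur relative to ∆IC?**

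- *∆IC*: spans baseline to the last wave.
- *IADL*: read as written, Eligibility keeps out people with significant loss at baseline, and the Cox paragraph treats IADL loss as an incident event. The loss therefore falls inside the ∆IC interval, and baseline IADL would have little or no variation to use as a predictor.
- *Death*: can only be a follow-up event, and leaves no last-wave index.
- *Falls*: undated. The past-year item asked at baseline precedes ∆IC; asked at follow-up, or taken as the incident event of the Cox model, it does not.

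Two of the three predictors cannot precede the change that they are meant to explain. The third does so only under a reading that the text does not state.

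**2. What would the reversed model show if the events did nothing to IC?**

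Assumed: 30% decline; fall risk 20% without decline; risk ratio 1.91 for decline against no decline; no effect of falls on IC.

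- Fall risk with decline = 0.20 × 1.91 = 0.382
- Odds ratio = (0.382/0.618) / (0.20/0.80) = 2.47
- Declined among fallers = 0.3 × 0.382 / (0.3 × 0.382 + 0.7 × 0.20) = 0.1146/0.2546 = 45%
- Declined among non-fallers = 0.3 × 0.618 / (0.3 × 0.618 + 0.7 × 0.80) = 0.1854/0.7454 = 25%
- With risk ratio 1.3: (0.26/0.74) / (0.20/0.80) = 1.41

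The values 1.91 and 1.3 are borrowed from Table 1 (functional loss) and Table 2 (death). There they compare low with higher IC level. They are not estimates for falls or for decline.

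**3. The same question with a continuous change.**

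Simulation with 5,500 people, 300 runs per setting, event risk about 5%, events caused by IC change, and no effect of events on IC:

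| Assumed odds ratio of event per SD of decline | Mean difference in ∆IC, event v no event | Runs significant at 5% | Runs significant for an unrelated baseline event |
|---|---|---|---|
| 1.3 | 0.26 SD | 99% | 4% |
| 1.7 | 0.52 SD | 100% | 5% |
| 1.91 | 0.63 SD | 100% | 7% |

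A predictor from the same interval gives a clear signal without causing anything. A baseline event unrelated to IC gives roughly the nominal rate.

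**4. How many would lack ∆IC through death?**

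Inputs from the sample size section and Table 2: 2,750 per group, unexposed mortality 0.04826, risk ratio 1.66, hence exposed mortality 0.04826 × 1.66 = 0.0801. The time unit of the rate is not stated, so both readings are shown.

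- As a 3-year risk: 2,750 × 0.04826 + 2,750 × 0.0801 = about 353
- As an annual risk: 2,750 × (1 − 0.95174³) + 2,750 × (1 − 0.9199³) = about 989

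**The case against.** The case on the other side is substantial.

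- The ∆IC regression is offered as something the authors should also be able to do, after the Cox and logistic models for the main question. It claims no causal effect, and a concurrent regression is legitimate if reported as one. This stands and limits the weight of the point. It does not give the model any use for finding determinants.
- A reader might infer that no analysis of decline runs forward in time. The documents do not support that. The section on quality of life and leisure-time activity regresses decline (DIC) on baseline quality of life, and then relates leisure-time activity to IC or DIC. Only quality of life is expressly dated at baseline, and DIC is binary, but a forward model of decline exists.
- Falls may be the baseline item, and the phrase about a last follow-up wave leaves intermediate waves possible. So it is not established that the order of falls and IC change must be unknown. The fair criticism for falls is that the timing is not stated. For IADL loss and death the objection does not help.
- The Discussion says that "the cohort study guarantees the maintenance of a temporal sequence between exposure to risk or protective factors and healthcare outcomes". A reader might take the ∆IC model as contradicting this. The sentence describes the cohort design in general, and the Cox model with baseline IC terciles keeps that order. The ∆IC model simply does not use this advantage.
- The wording of objective 6 may be a slip. That is likely, but it is a numbered objective and should say what is meant.

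**Conclusion.** The point holds, limited to two items: the wording of objective 6 and the choice of X in the optional ∆IC regression. As specified, that regression yields a concurrent association that the study's own hypothesis would generate even if the events had no effect on IC, so it cannot separate drivers of decline from its consequences. Including death adds a second fault, because those who die have no ∆IC.

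The documents do not fix the size. It would be tempting to quote the odds ratio of 2.5 as the bias that follows from the plan's own risk ratios. That is not supported: the 20% and 30% are assumptions, and the borrowed ratios concern other outcomes and another contrast. Because an odds ratio is symmetric, 2.5 only restates the assumed forward association seen from the other side. The argument from time order does not depend on these values. It does depend on reading Eligibility as excluding baseline IADL loss. The main analyses of baseline IC terciles as a predictor are not affected.

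**What to change.** 1. Reword objective 6 as the effect of baseline predictors on later IC change.
2. In the ∆IC model, replace X with factors measured at or before baseline: falls and hospitalizations in the year before entry, leisure-time physical activity, WHODAS, social capital, and sociodemographic and clinical factors. State the wave for each.
3. Remove death from X and say how people who die before the last wave are handled when ∆IC is the outcome.
4. Report IC change by incident IADL loss or falls only as a concurrent, descriptive association. The same section already plans to tabulate IC measures by levels of ADL/IADL, falls and death, so no new analysis is needed.

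The cost is the wording of one objective and one model paragraph. The variables are already on the study's lists, so no new measurement is needed provided that the past-year falls and hospitalization items are asked at baseline.
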